#### Withdrawal criteria

Participation in the study is voluntary. There are no negative consequences for non-participation or dropping out. Individuals who refuse participation or drop out get medical and psychosocial care as usual. Although an increase of suicidality is not expected during treatment, participants will be withdrawn from the study by the research team in case of heightened suicidality.

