#### Assessment of safety

Participants will be regularly screened for suicidality. In case of increased suicidality - although not expected - participants will be taken out of the study by the research team. For safety and for keeping an overview over the study, a case report form (CRF) will be completed after each information, assessment or therapy session. The CRF contains checklists, test results, information about the participant (other therapies, medications, problems etc.), adverse events, date of the assessments and name of the investigators.

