#### Methods against bias

The proposed study requires several methods to avoid bias.

Selection bias: The randomisation procedure is the gold standard to avoid this bias. Random numbers will therefore be generated in advance. The randomisation procedure will be controlled by comparing the two groups with regard to possible confounders, i.e. age at the time of trauma, gender, educational level, diagnosis, cognitive status and trauma severity.

Detection bias: The baseline assessment is done before randomisation to avoid this bias. In addition, the therapists will not collect any outcome data at posttest and follow-up. This will be done by blinded members of the research team (clinical psychologists or psychiatrists or advanced master students in clinical psychology).

Performance bias: To counteract this bias, the standardisation procedure (manual, extensive training, documentation of sessions, supervision) is established.

Attrition bias: Statistical analysis will include techniques to minimise possible attrition bias, i.e. intention-to-treat analysis and imputing missing data. In case of drop-outs, it is intended to continue data collection whenever possible.

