#### Handling of missing values and drop-outs

A complete data set is available if all three test times (pretest, posttest, follow-up) have been performed. A drop-out can occur, (1) if the participant does not complete the pretest, (2) decides after information or after randomisation against participation, or (3) starts with the treatment, but discontinues it.

If less than 20% of the items of one self-report instrument are missing, missing values are imputed by the mean of the scale of this participant. If a whole scale is missing, the value will be imputed by the expectation-maximation (EM) algorithm.

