#### Consent

Consent to joining the study will be requested from each participant only after a full verbal and written explanation has been given, an information leaflet offered and time allowed for consideration; such declarations of consent will be signed. The right of the participant to refuse to participate without giving reasons will be respected.

After the participant has entered the study, the clinician will remain free to provide alternative treatment to that specified in the protocol at any stage if he/she feels it is in the participant’s best interest, but the reasons for doing so will be recorded. In these cases, the participants remain within the study for the purposes of follow-up and data analysis. All participants are free to withdraw at any time from the treatment without giving reasons and without prejudicing further treatment.

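### Heightened suicidality takes participants out of the study rather than out of study treatment only, so outcomes may be lost for a reason linked to a primary endpoint

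*Protocol article*

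**What the plan says.** All references are to the protocol article.

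- **Withdrawal criteria:** "participants will be withdrawn from the study by the research team in case of heightened suicidality".
- **Assessment of safety:** "Participants will be regularly screened for suicidality", and if suicidality increases, "participants will be taken out of the study by the research team". Both sections add that an increase is not expected.
- **Consent:** after entry, "the clinician will remain free to provide alternative treatment to that specified in the protocol at any stage" if this is in the participant's best interest. The consequence is then stated: "In these cases, the participants remain within the study for the purposes of follow-up and data analysis".
- **Methods against bias (attrition):** the plan is "intention-to-treat analysis and imputing missing data", and further, "In case of drop-outs, it is intended to continue data collection whenever possible".
- **Handling of missing values and drop-outs:** three drop-out routes are listed: an incomplete pretest, a decision by the participant not to take part, and a participant who "starts with the treatment, but discontinues it". A scale that is missing as a whole is imputed by EM.
- **Study outcome measures:** PTSD and depressive symptoms are the primary endpoints. Outcomes are measured at pretest, posttest and follow-up.

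**The concern.** Stopping a therapy for safety and stopping outcome assessment are separate decisions. The article draws this line itself in the Consent section, where a participant may leave the treatment and where a change of treatment does not end follow-up. The suicidality rule does not draw it: it ends study participation.

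The participants concerned are not a random subset. Rising suicidality is plausibly tied to depressive symptoms, so the outcomes lost would tend to be poor ones. EM normally assumes that missingness depends only on observed data. A pretest taken before the deterioration cannot show it, so the imputed scores may be too favourable. If more participants are removed from one arm than the other, the arm difference moves. More removals from the LRT arm would flatter LRT; more from the control arm would work against it.

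There is also a practical question for the site. No sentence says which rule governs a participant who becomes suicidal and is moved to other care.

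**Working it through.** **1. Do the rules collide?**

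| | Suicidality rule (Withdrawal criteria, Assessment of safety) | Change-of-treatment rule (Consent) |
|---|---|---|
| Trigger | heightened suicidality | clinician chooses other treatment |
| Who acts | research team | clinician |
| Consequence | leaves the study | stays in follow-up and analysis |

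The triggers and actors differ, so there is no general contradiction. The rules meet in one case: a suicidal participant who is also referred to other treatment. That case is foreseeable, and the two rules then give different answers.

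**2. Does the attrition text already cover it?** The intention to continue data collection applies to drop-outs. Of the three listed routes, discontinuing a started treatment can fit an LRT participant whose therapy is stopped. It fits a social-club control less well. No route names withdrawal by the research team. So coverage is possible but not clear, and least clear in the control arm.

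**3. What is lost on the literal reading?** Withdrawal before posttest loses 2 of 3 assessments. Withdrawal between posttest and follow-up loses 1 of 3 and leaves the posttest comparison untouched.

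**4. How large could the effect be?** The plan gives no expected number of such withdrawals, so there is no figure of its own to reproduce on this point. Inputs from Sample size: 40 per arm at enrolment, 25 per arm required, d = 0.7. Assumed inputs: net imbalance between arms k = 0, 1 or 2; gap between true and imputed score of 0.5 to 1.5 SD, taken as equal for all affected participants.

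Shift in arm difference = k × gap / 40, in SD units; the share of d is the shift divided by 0.7.

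| k | gap 0.5 SD | gap 1.0 SD | gap 1.5 SD |
|---|---|---|---|
| 0 | 0 | 0 | 0 |
| 1 | 0.0125 (1.8% of d) | 0.025 (3.6%) | 0.0375 (5.4%) |
| 2 | 0.025 (3.6%) | 0.05 (7.1%) | 0.075 (10.7%) |

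Against sampling error:

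- With 40 per arm, SE = √(2/40) = 0.224 SD. The shift is 0.06 to 0.17 SE for k = 1 and 0.11 to 0.34 SE for k = 2.
- With 25 per arm, SE = √(2/25) = 0.283 SD. The same shifts are 0.04 to 0.13 SE and 0.09 to 0.27 SE.

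Precision is not the issue. The plan already allows for 80 − 50 = 30 losses, and one or two more change little. What sets these losses apart is that they depend on outcome.

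**The case against.** The strongest reply has four parts.

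- **The rule is protective.** Taking very old, multiply traumatised people in crisis out of research procedures is defensible and fits the exclusion of acute suicidality at entry. This stands, and any fix must keep the clinical safeguard. It does not require that assessment ends in every case.
- **The attrition text may be enough.** The sentence on continued data collection is not restricted to drop-out initiated by the participant. This stands in part: it may reach these cases, but a rule that takes someone out of the study points the other way.
- **This is detail that an article leaves to the full protocol.** This does not stand. The article states the removal rule twice and a retention rule once, so the point concerns what is written. An analysis plan cannot recover assessments that were not taken.
- **The mechanism and size are assumed.** This stands. The article does not say which variables enter the EM model, and case report forms completed after sessions may hold later information. Adverse-event recording would still capture the event itself.

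A reader might also infer that the rule contradicts the intention-to-treat commitment. The document does not support that, because intention-to-treat is paired there with imputation and with continued data collection. Nor does it support reading the Withdrawal criteria and the Consent section as flatly contradictory, since they overlap only in the case set out above.

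**Conclusion.** The point holds as a minor one. As worded, the suicidality rule removes participants from the study itself and, read literally, stops outcome assessment for a reason plausibly linked to a primary endpoint. It can overlap with the Consent rule without either giving way, and the attrition text does not clearly resolve this.

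The likely bias is small, and its size cannot be derived from the document. The range of 0.0125 to 0.075 SD for a net imbalance of one or two participants rests on assumed counts and gaps, and on imputation that carries no information about the deterioration. The shift is zero if numbers and gaps are equal in the two arms. A reader might infer a material threat to the trial's conclusions; neither these figures nor the protocol's expectation that suicidality will not increase supports that. The case for acting is that the change is cheap and follows the approach the plan already takes elsewhere.

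**What to change.** In Withdrawal criteria and in Assessment of safety, replace removal from the study with the following:

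- heightened suicidality leads to stopping or changing study treatment, with clinical referral;
- posttest and follow-up are still sought, with continuing consent and if the clinician judges them bearable;
- the participant is analysed in the randomised arm.

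In Handling of missing values and drop-outs, add withdrawal by the research team as a named case for both arms, so that the stated intention to continue data collection clearly applies to it.

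The cost is two or three sentences, a little extra tracing by the existing assessors, and a clinical judgement before each assessment on whether a participant in crisis can bear it.

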#### Informed consent

The objects and goals, detailed information about assessment and therapy as well as the procedure of randomisation will be explained to the subjects. The information will also be given in printed form for the subjects. Written informed consent will be obtained from all participants prior to inclusion. Participants who cannot give their informed consent will not be included in the study.

#### Sample size

Previous studies on PTSD treatments found a large mean effect size for PTSD outcomes (controlled *d* = 0.8 with a supportive control group) [26]. Studies on LRT also found a large mean (pre-post) effect size in older individuals with a mental disorder (in most studies depression) (g = 1.3; 19). We rest our sample size calculation on the conservative assumption of a medium-to-large effect size (d = 0.7, corresponds to f = 0.35). The sample size was calculated using G*Power 3.1.0 [27]. Given an α = 0.05 and a test power 1-β = 0.80, a total sample size of *n* = 50 (each group *n* = 25) is required. We assume a rather conservative drop-out rate of about 40% from enrolment to follow-up. Thus, we propose to start with 80 participants at enrolment (i.e. 40 in the LRT and 40 in the control group).

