**Methods:**

The main goal of this study is to evaluate the effect of LRT for Holocaust survivors (LRT-HS) on symptoms of PTSD and related mental health problems (depression, anxiety, prolonged grief), compared to a supportive control group. A secondary goal is to identify the characteristics of participants that seem to especially benefit from the treatment. The proposed study is a randomised, controlled follow-up trial including Holocaust survivors with one or more trauma-related disorders. The LRT treatment consists of 20–25 sessions. Before and after the treatment phase, participants in both conditions will be assessed. Follow-up will take place 6 months after the treatment. A sample size of 80 is required (drop-out rate included).

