We expect that life-review therapy will reduce the symptoms of PTSD and related mental health problems with a large pre-post effect size and to a greater extent than the supportive control group at posttest and 6-months follow-up with a medium-to-large effect size.
2.Which factors moderate the treatment effect, i.e. which factors influence who benefits most from the intervention?

We expect that LRT-HS will have a greater effect in people (a) with more severe symptoms of PTSD, depression, anxiety and/or grief at pretest, (b) with lower positive well-being and posttraumatic growth at pretest, (c) of female gender, (d) with higher cognitive status at pretest, (e) with higher trauma severity, i.e. number of traumatic events, months/years experienced during the Holocaust, as well as traumatic experiences before and after the Holocaust.

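### The sample-size figures do not fit together: 80 enrolled with 40% loss leaves 48, not the required 50, and the inputs given do not yield 50 for a plain two-sided two-group comparison

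*Protocol article*

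**What the plan says.** The Sample size section of the protocol article takes a "medium-to-large effect size (d = 0.7, corresponds to f = 0.35") as its planning value. It says "The sample size was calculated using G*Power 3.1.0" and, with alpha set at 0.05, gives the result as: "a test power 1-β = 0.80, a total sample size of *n* = 50 (each group *n* = 25) is required". It then states "We assume a rather conservative drop-out rate of about 40% from enrolment to follow-up" and concludes that 80 should be enrolled, 40 per group. The abstract repeats the conclusion: "A sample size of 80 is required (drop-out rate included").

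The section does not say which G*Power procedure was used, whether the test is one- or two-sided, how many measurements enter it, or what correlation was assumed.

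The hypothesis under Study objectives is that LRT will reduce symptoms "to a greater extent than the supportive control group at posttest and 6-months follow-up with a medium-to-large effect size". The Statistical analysis section plans ANOVAs with covariates (age at trauma, gender, education, cognitive status, trauma severity), followed by growth-curve and multivariate analyses. The pretest score is not among the listed covariates.

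**The concern.** There are two separate problems.

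The first is internal. A requirement of 50, a loss of about 40% and an enrolment of 80 cannot all hold, because 80 patients less 40% is fewer than 50. No choice of test enters this.

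The second is whether 50 follows from the inputs printed beside it. The conversion of d = 0.7 to f = 0.35 is the two-group one (f = d/2), the planned ANOVA uses a non-directional F test, and no one-sided alpha is declared. The hypothesis is a between-group difference at posttest and at follow-up. Read plainly, this is a two-sided comparison of two groups at one time point, and 50 is too few for 80% power in that comparison.

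Readers will use the 80% figure when they interpret a non-significant result. If the operative test is the plain one, the chance of missing the planned effect at follow-up is about one in three, not one in five.

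**Working it through.** **Inputs.** From the Sample size section: d = 0.7, f = 0.35, alpha 0.05, power 0.80, N = 50, drop-out 40%, enrolment 80. From Randomisation: 1:1 allocation. Every correlation below is an assumption, because the article gives none.

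**1. Drop-out step.**
- Patients left: 80 × (1 − 0.40) = 48, or 24 per group.
- Enrolment needed to keep 50: 50 / 0.60 = 83.3, so 84 with equal groups.
- Largest loss that leaves 50 of 80: 1 − 50/80 = 37.5%.

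**2. Can N = 50 be reproduced?** With inputs added, nearly or fully:
- Repeated-measures between-group F test, λ = f²·N·m / (1 + (m − 1)ρ) on 1 and N − 2 degrees of freedom. With m = 2 and ρ = 0.5, λ = 0.1225 × 50 × 2 / 1.5 = 8.17 and power is 79.96%. With m = 3 and ρ = 0.6, λ = 0.1225 × 50 × 3 / 2.2 = 8.35 and power is 80.8%.
- ANCOVA on the pretest score, λ = f²·N / (1 − r²) on 1 and N − 3 degrees of freedom. With r = 0.5, λ = 6.125 / 0.75 = 8.17 and power is 79.9%.
- One-sided t-test, 25 per group: 78.7%; 26 per group (52 in total) are needed for 80%.

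**3. The plain reading.** Two-sided two-sample t-test (equivalently a one-way ANOVA with f = 0.35), noncentrality d·√(n/2) on 2n − 2 degrees of freedom:

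| n per group | noncentrality | power at d = 0.7 | d detectable with 80% power |
|---|---|---|---|
| 24 | 0.7 × √12 = 2.42 | 66.1% | 0.83 |
| 25 | 0.7 × √12.5 = 2.47 | 67.9% | 0.81 |
| 34 | 0.7 × √17 = 2.89 | 81.2% | – |

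The exact requirement for 80% power is 34 per group, 68 in total.

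**4. The same tests with the 48 patients left.**

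| Test (correlation assumed) | Power at N = 48 |
|---|---|
| Two-sided t, unadjusted, one time point | 66.1% |
| One-sided t, unadjusted, one time point | 77.2% |
| Repeated measures, m = 2, ρ = 0.5 | 78.3% |
| Repeated measures, m = 3, ρ = 0.6 | 79.2% |
| Repeated measures, m = 3, ρ = 0.5 | 82.8% |
| ANCOVA, r = 0.5 | 78.2% |
| ANCOVA, r = 0.6 | 84.3% |
| ANCOVA, r = 0.7 | 91.3% |

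**The case against.** The strongest reply is that no test is named, so the unadjusted two-sided comparison is the reviewer's benchmark and not the authors'. The article plans ANOVAs with covariates and three assessments. Several ordinary procedures reach about 80% with 50 patients, and one of them, ANCOVA on the pretest, is a comparison at a single time point. This stands. A reader might infer that 50 patients cannot give 80% power, or that power at follow-up simply is 66%. The document supports neither statement: 66% is the least favourable of the readings computed, and it holds only for an unadjusted, two-sided test at one time point.

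The reply does not make the printed figures sufficient. The routes that reach about 80% need a correlation, or a one-sided test, that the article does not state. The listed covariates do not include the pretest score. The three-measurement version includes the pretest, which is taken before randomisation. No group difference is expected there, so if d = 0.7 applies only at the later assessments, averaging over all three weakens the contrast.

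A second reply is that the drop-out gap is only two patients and the rate is given as approximate. The article also counts patients who discontinue treatment as drop-outs, intends to go on collecting their data, and plans intention-to-treat analysis with imputation, so 40% drop-out need not mean 40% missing outcomes. This makes the gap small, and 48 is not a certain evaluable number. But the section itself uses 40% as the loss between enrolment and the evaluable total, and on that use 80 falls short of 50. Imputation does not restore the information lost with a patient who has no outcome.

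A third reply is that a journal article may leave the G*Power settings to a fuller document. That would excuse silence about them. It does not excuse an enrolment figure that disagrees with the requirement and loss rate in the same paragraph.

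**Conclusion.** The point holds in two parts of different strength.

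- **Drop-out step: wrong as written.** 80 enrolled with 40% loss gives 48, two short of the 50 called required. This rests only on the section's own figures and on treating drop-outs as not evaluable, as the section does.
- **Power claim: not supported by the inputs printed.** For an unadjusted two-sided comparison at posttest or follow-up, d = 0.7 needs 68 patients. Power is 67.9% with 50 and 66.1% with 48. About 80% with 50 requires unstated inputs. The two-measurement test with correlation 0.5 and the pretest-adjusted test with r = 0.5 both fall to about 78% with 48. More favourable assumed inputs exceed 80% with 48, for example pretest adjustment with r = 0.6.

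This is not a finding that the trial is underpowered. Whether it is depends on a test and a correlation that the article does not give.

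**What to change.** Keep 80 patients and rewrite the Sample size paragraph and the matching sentence in the abstract:

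- State that 40% loss from 80 leaves 48, 24 per group, and do not present 80 as covering a requirement of 50.
- Name the G*Power procedure, the sidedness, the time point or points, the number of measurements and the correlation used.
- Restate power for 48 patients on that basis. If the primary comparison is unadjusted, two-sided and at one time point, it is about 66% for d = 0.7, and 80% power is reached at d = 0.83. If the primary analysis adjusts for the pretest score, say so in the Statistical analysis section and give about 78%, 84% or 91% for an assumed correlation of 0.5, 0.6 or 0.7.

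The change is to wording only and needs no further recruitment. The cost is a less favourable stated power, unless pretest adjustment with a correlation above about 0.5 can be justified.

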### Randomisation

After providing informed consent and receiving a baseline assessment, the participants will be individually assigned to a group at random. The allocation ratio for randomisation into either the treatment or control group is 1:1. The randomisation will be performed by a randomization list that was generated by a computer programme (RandList) beforehand, independently operated by the principal investigator at the University of Siegen, Germany, who does not have any personal contact with the participants. The results of the randomization will be sent to the study coordinator in Jerusalem, Israel, who will contact the therapist to explain the next steps.

### Interventions

#### Life-review therapy

The LRT-HS applied in this study includes six modules.
Module 1, “Introduction and motivation, diagnostics and goal setting”, includes an introduction into life-review therapy (i.e. rationale, tools, life book), an assessment of symptoms, diagnostics and individualized goal setting.Module 2, “Structured life review”, is one of two the main parts of the therapy. The structure and content of this life review is adapted from that presented by Haight and Haight [22], which has already been applied with older trauma patients [21]. Four phases can be distinguished: childhood (2 sessions), adolescence (1 session), adulthood (2 sessions) and integration (2 sessions).Module 3, “Narrative confrontation with the stressor”, is the second of the two main parts of the therapy. This module is positioned in between the sessions of module 2, exactly *before* the session in which the life phase is discussed in which the traumatic event has happened. If the Holocaust happened during the childhood, module 2 starts with the early childhood (birth until Holocaust), followed by module 3 (Holocaust experiences), and followed by the rest of module 2. This form of narrative exposure has been proven to be effective in the treatment of PTSD [13, 21, 28].Module 4, “Examining stuck points”, continues with cognitive aspects of the integration sessions of the life review. It addresses dysfunctional thoughts that the patient often ruminates about and helps him/her to change them into helpful ones. Two strategies are used: Socratic dialogue in order to help the patient to challenge dysfunctional thoughts and formulate new, helpful thoughts, and a letter to the child/adolescent/young adult that the patient has been when he/she experienced the Holocaust.Module 5, “Recapturing life”, focuses on changes in behaviour (social contacts, pleasant activities) that have already been stimulated by life review and are continued in this module.Module 6, “Closing the therapy”, is the final session with a review of the therapy sessions and a planning of the next steps after therapy.

Session duration is usually 50 min (most sessions) or 60–90 min (module 3). The interventions are described in Table 1 in more detail.

**Table 1 Tab1:** Description of sessions

Session no.	Topic	Therapeutic strategies
Module 1: Introduction and motivation, diagnostics and goal setting		
1	Introduction and motivation	Introduction to and rationale of life review; tools (photos and other objects); life book; organizational issues
2	Diagnostics	Diagnostic investigation of symptoms, resources and social factors; overview over biography (“timeline”)
3	Goal setting	Setting individual goals; preparation for first life review session
Module 2: Structured life review		
4–5	Childhood	Questions on childhood; life book
6	Adolescence	Questions on adolescence; life book
7–8	Adulthood	Questions on adulthood; life book
9–10	Integration	Summary and integration questions
Module 3: Narrative confrontation with the stressor		
11	Pre-Holocaust experiences	Getting an overview about the experiences; clarifying the context of a single event; details of a single event; ending the narrative; making meaning of the event (often in the following session)
12–13	Holocaust experiences	Getting an overview about the experiences; clarifying the context of a single event; details of a single event; ending the narrative; making meaning of the event (often in the following session)
14	Post-Holocaust experiences	Getting an overview about the experiences; clarifying the context of a single event; details of a single event; ending the narrative; making meaning of the event (often in the following session)
Module 4: Examining stuck points		
15	Identifying stuck points	Identifying functional and dysfunctional thinking in four domains; maybe beginning the discussion of dysfunctional thoughts
16	Discussing dysfunctional thoughts	Challenging dysfunctional thoughts (e.g. Socratic dialogue); formulating functional thoughts; introducing the exercise of writing a letter to the child-self
17	Letter to the child-self	Reading the letter out loud; summarising the most important insights and conclusions for the future
Module 5: Recapturing life		
18	Social contacts	Sharing biographic events and insights; reading the trauma narrative to relatives; maybe handing over the biography to relatives
19	Pleasant activities	Individual list of pleasant activities; planning activities; discussing problems with pleasant activities
Module 6: Closing the therapy		
20	Concluding session	Re-examining goals; evaluation of interventions; planning the future

Standardization of procedures: Therapists use a manual of this LRT-HS, which includes descriptions of the content of each session and material for the sessions. Because of the research setting, therapists will document what happens during the sessions in detail on checklists, i.e. which interventions they had applied and whether (and why) they had stressed one point more than another. Working sheets and interview guidelines are included in the manual as well. Adherence to the treatment manual is ensured by the intensive training before the intervention phase, the regular supervision and the examination of the session documentations.

Psychotherapists: The LRT-HS will be administered by trained psychotherapists, i.e. psychologists, psychiatrists and clinical social workers. All psychotherapists have a master’s degree in psychology, medicine or clinical social work. Furthermore, all participating psychotherapists will be trained for this intervention by a panel of experts and supervisors in the field of psychotherapy for older age (Dr. [name], Dr. [name], Dr. [name], Dr. [name]). A two-day workshop will precede the intervention phase. Supervision sessions will take part every month (i.e. about 5 sessions per patient). All sessions will be documented in a structured form and will be reflected upon in the supervision sessions.

Pilot data: We applied the described treatment programme with a few participants and found that they accepted it and rate the treatment as very helpful. In addition, symptoms were reduced to a clinically significant degree.

